## Assignment of interventions: blinding

6

### Who will be blinded?

6.1

Specifically, researchers responsible for evaluating the outcomes of the study will not have knowledge of the participants’ group assignments, ensuring that assessments are conducted objectively and impartially. Similarly, the researchers who perform data analysis will be kept unaware of the group assignments. The data will be encoded and kept concealed throughout the analysis phase until its conclusion. Through these measures, we aim to reduce potential bias by ensuring that those assessing outcomes and analyzing data do not have preconceived notions about the participants’ intervention groups.

### Procedure for unblinding if needed

6.2

Unblinding in this study is permitted under specific circumstances that warrant such action. These circumstances include emergency medical needs, where a participant experiences a serious adverse event or requires urgent medical intervention, and the knowledge of the group assignment is crucial for their treatment. Additionally, after the study concludes, requests for unblinding based on valid medical reasons by the participant or their healthcare provider will be considered. The procedure for unblinding involves a written request by the principal investigator or a member of the clinical oversight team. The clinical review panel is responsible for reviewing all unblinding requests to assess if the conditions for unblinding are met. Upon approval, the research team will follow a predefined protocol to disclose the participant’s group assignment safely. This protocol is designed to ensure that the unblinding process does not adversely affect the study’s integrity or the participant’s welfare, adhering to ethical guidelines and preserving the scientific value of the research.

## Data collection and management

7

### Plans for assessment and collection of outcomes

7.1

All questionnaires and assessment tools that will be used in this study have been validated for reliability and validity in previous studies. Cerebral cortex conditions will be acquired with standardized fNIRS and EEG equipment. All assessors will receive specialized training to ensure consistency and accuracy of assessments. Data entry will be performed using an electronic data capture (EDC) system and regular data quality audits will be implemented.

### Plans to promote participant retention and complete follow-up

7.2

The follow-up of this study is scheduled 4 weeks after the end of the intervention. Regular contact will be maintained with participants by phone, email, or text message to provide study progress updates, answer participant questions, and remind of upcoming follow-up visits.

### Data management

7.3

All data will be entered through the EDC system and a Unicode scheme will be used to maintain anonymity. Data will be stored on a password-protected server, accessible only to authorized researchers. Regular data backups will be performed to prevent data loss or corruption.

### Confidentiality

7.4

All personal information, including name, gender, age, educational level, and medical history, will initially be collected. However, to ensure participant confidentiality, all identifying information will be de-identified after collection. This process involves replacing personal identifiers with unique codes. Only a limited number of authorized research team members will have access to the key linking these codes to the actual identifiers, which will be stored separately and securely. We will not share any personal information with third parties without obtaining explicit consent from the participant. All members of the research team will be required to sign a confidentiality agreement to uphold privacy standards. Throughout the study and after its conclusion, all personal information will be securely stored on a server accessible only to authorized researchers. We will implement appropriate technical and organizational measures to safeguard the data against unauthorized access, disclosure, or loss.

### Plans for collection, laboratory evaluation and storage of biological specimens for genetic or molecular analysis in this trial/future use

7.5

This clinical trial does not involve the collection, laboratory evaluation, or storage of biological specimens (e.g., blood, tissue, etc.) for genetic or molecular analysis.

## Statistical methods

8

### Statistical methods for primary and secondary outcomes

8.1

Data analysis will be performed using SPSS 26.0. All data will be described by mean ± standard deviation (X ± S), with P < 0.05 considered statistically significant. Descriptive statistics will summarize the data. Confidence intervals and effect sizes will be reported where applicable, focusing on feasibility as the primary outcome and clinical measures as secondary outcomes.

#### Primary outcome analysis: feasibility metrics

8.1.1

Recruitment, adherence, and completion rates will be the focus, analyzed descriptively to provide insights into the practical implementation and scalability of the intervention. Each metric will be reported as a percentage:

- Recruitment rate: Proportion of eligible participants who were successfully recruited.

- Intervention adherence: Proportion of participants who adhered to the intervention throughout the study.

- Assessment completion: Proportion of participants who completed all assessments and follow-ups.

- Safety assessment: Safety will be evaluated through subjective and objective measures, including monitoring vital signs and documenting adverse reactions.

#### Secondary outcome analysis: clinical measures

8.1.2

- Measures such as PHQ-9, HADS, MMSE, PSQI, and SS-QOL will be summarized at each time point using descriptive statistics to observe potential effects and trends. Given the limited sample size, inferential analysis will be avoided. Instead, the focus will be on descriptive statistics and comparison with minimal important changes (MIC) to assess the clinical relevance of observed changes.

- To compare the efficacy of aromatherapy versus CBT, non-inferiority tests will be conducted to determine if the efficacy of aromatherapy is not significantly worse than that of CBT. The non-inferiority margin will be defined *a priori*, typically set at a 10% margin, indicating that aromatherapy is considered non-inferior if the difference in improvement between CBT and aromatherapy falls within this margin. If assumptions for parametric tests are violated, descriptive statistics will be used to summarize the data. This analysis will highlight the potential of aromatherapy as an effective complementary therapy.

- EEG data will be processed using a bandpass filter (0.6-46 Hz) and artifacts will be removed using Independent Component Analysis (ICA). A minimum of 4 minutes of artifact-free data will be selected for further analysis. The Lempel-Ziv Complexity (LZC) values for the full frequency band (0.6-46 Hz) and specific bands: δ (1-3.5 Hz), θ (4-7 Hz), α (8-13 Hz), and β (13-30 Hz) will be summarized at baseline, post-intervention, and follow-up within each group. Changes in LZC values over time and between groups will be explored descriptively, and the relationship between changes in LZC values and improvements in PHQ-9 scores will be examined using Pearson correlation to identify potential correlations between EEG biomarkers and clinical measures of depression. This analysis will help to understand if EEG changes can be predictive of or associated with improvements in depressive symptoms, providing preliminary insights into the neurological impacts of the interventions.

- The fNIRS data will collect information on changes in oxygenated hemoglobin (HbO) and deoxygenated hemoglobin (HbR) concentrations in the prefrontal lobe and part of the temporal lobe during the Verbal Fluency Task (VFT). The VFT will consist of a 30-second pre-task baseline, a 60-second task period, and a 70-second post-task baseline to assess changes in regional brain activity and forebrain functional network connectivity. The fNIRS data will be preprocessed to remove artifacts, with baseline correction performed using the moving average method. The last 10 seconds of the pre-task period and the first 55 seconds of the post-task period will be used for baseline correction. Descriptive statistics will summarize the integral values of HbO and HbR across different groups and time points. Changes in HbO and HbR values over time and between groups will be explored descriptively, and the relationship between HbO values and PHQ-9 scores will be examined using Spearman’s rank correlation.

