## Objectives

2

The objectives of this study are:

To assess the feasibility of implementing the mixed herb aromatherapy intervention in a clinical setting. Key metrics include recruitment rates, adherence rates, completion rates and safety assessment.To gather preliminary data on the efficacy of mixed herb aromatherapy on PSD, including symptom relief and improvements in the quality of life of the patients.To compare the preliminary effects of aromatherapy versus routine treatment and CBT for PSD patients, focusing on differences in symptom recovery and sustainability of treatment effects.To explore the impact of aromatherapy on brain function assessments (EEG and fNIRS) and its correlation with the recovery of patients suffering from PSD. This study will utilize EEG and fNIRS to assess the impact of aromatherapy on brain function in PSD patients and investigate the correlation between these brain function changes and the recovery progress of the patients.

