### Sample size and feasibility criteria

4.5

Since this study employs a novel mixed herbal aromatherapy intervention, there is no prior research directly comparable to reference. As this is a pilot RCT, the focus is on assessing the feasibility of the intervention rather than hypothesis testing. Therefore, the sample size estimation is not based on power analysis but according to rule of thumb.

Based on the guidance from Billingham et al. (49), a sample size of approximately 30 participants per group is considered appropriate for a pilot study. This sample size is justified by the need to gather preliminary data on feasibility outcomes, such as recruitment rates, adherence rates, and completion rates, and to ensure sufficient variability and precision in the estimates.

Taking into account 10% potential dropout rates, we will aim to recruit approximately 33 participants per group to ensure we have enough data for the feasibility analysis. This will result in a total sample size of approximately 99 participants across the three groups.

The predefined criteria for feasibility outcomes are:

- Recruitment rate of at least 70%: This is considered a reasonable and achievable target for pilot studies to ensure adequate participant recruitment.

- Adherence rate of at least 80%: This reflects a high level of participant engagement and compliance with the intervention protocol, which is crucial for obtaining reliable data.

- Completion rate of at least 85%: This indicates that the majority of participants complete the study, ensuring data integrity and minimizing the impact of dropouts on the study results.

These criteria will help determine the feasibility of conducting a full-scale RCT.

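### The clinical scales are judged by change against an MIC, with no baseline-adjusted aromatherapy-minus-control difference, so the planned analysis cannot show added benefit over routine care

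*Protocol article*

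**What the plan says.** Section 8.1.2 of the protocol article summarises PHQ-9, HADS, MMSE, PSQI and SS-QOL descriptively at each time point, sets inferential analysis aside because the sample is small, and states that "the focus will be on descriptive statistics and comparison with minimal important changes (MIC) to assess the clinical relevance of observed changes". It gives no MIC values. The one between-arm comparison it names for efficacy is the non-inferiority test of aromatherapy against CBT, on the difference in improvement, with no adjustment for baseline.

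Section 8.1 adds a general provision: "Confidence intervals and effect sizes will be reported where applicable". It does not say for which contrast.

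The third objective (section 2) is "To compare the preliminary effects of aromatherapy versus routine treatment and CBT for PSD patients". Section 4.2.1.1 gives the reason for the control group as measuring what CBT and aromatherapy add to standard care. PHQ-9 is an entry criterion with a cut-off of 5 (section 4.1.1.1) and also an outcome (section 4.3.2). The Discussion says that physical recovery may affect the course of post-stroke depression.

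**The concern.** The objective is comparative and the stated yardstick is not. A fall from baseline in the aromatherapy arm mixes any treatment effect with regression to the mean, natural recovery, the effect of the rehabilitation that all arms receive, and non-specific effects. The components shared by the randomised arms are expected to be equal across them. They cancel in a difference between arms and remain in full when an arm's change is set against an MIC.

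Two things are at stake. The control arm was included to isolate added benefit, but no estimate is specified that uses it. And a pilot meant to prepare a larger trial should supply the between-arm difference, its interval and a baseline-adjusted SD, all of which the collected data can give.

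**Working it through.** **The plan's own figure.** Section 4.5 starts from a rule of thumb: "a sample size of approximately 30 participants per group is considered appropriate for a pilot study". It then inflates: "Taking into account 10% potential dropout rates, we will aim to recruit approximately 33 participants per group". 30 × 1.10 = 33 and 3 × 33 = 99, as stated. 33 × 0.90 = 29.7, so about 30 per arm are evaluable, and n = 30 is used below.

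**What has to be assumed.** The protocol gives no SD, no correlation between baseline and follow-up, no source-population mean and no MIC value, and says that "there is no prior research directly comparable to reference". For illustration: source-population PHQ-9 normal with mean 7 and SD 5; correlation r between two measurements 0.5 to 0.7; selection on PHQ-9 ≥ 5 alone; baseline equal to the screening score; no treatment effect and no recovery; 5 points as a threshold for individual change.

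**1. Regression to the mean.** Expected fall = (1 − r) × SD × λ, with a = (5 − 7)/5 = −0.40 and λ = φ(a)/[1 − Φ(a)] = 0.368/0.655 = 0.562.

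| r | Mean fall (points) | Share falling ≥ 5 points |
|---|---|---|
| 0.5 | 0.5 × 5 × 0.562 = 1.40 | 22% |
| 0.6 | 0.4 × 5 × 0.562 = 1.12 | 18% |
| 0.7 | 0.3 × 5 × 0.562 = 0.84 | 13% |

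The fall depends on the source mean. With SD 5 and a cut at 4.5 (continuity correction), it is 1.54 (r = 0.5) or 0.93 (r = 0.7) points at mean 6, 1.03 or 0.62 at mean 8, and 0.63 or 0.38 at mean 10.

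**2. A fall common to all arms.** Ignoring selection, the share of individuals improving by 5 or more is 1 − Φ[(5 − d)/(SD × √(2(1 − r)))], where d is the shared mean fall. For SD 4 to 6 and r 0.5 to 0.8, this is 2 to 20% at d = 0 and 22 to 37% at an assumed d = 3, again with no treatment effect.

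**3. Precision.** Selection narrows the baseline spread. The baseline variance becomes k × SD² with k = 1 + aλ − λ² = 1 − 0.225 − 0.316 = 0.460, so the enrolled baseline SD is 5 × √0.460 = 3.4. In units of SD², the change score has variance (1 − r)²k + (1 − r²), and the baseline-adjusted outcome has 1 − r².

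| r | Change score | Adjusted | Variance saving |
|---|---|---|---|
| 0.5 | 0.25 × 0.460 + 0.75 = 0.865 | 0.75 | 13% |
| 0.6 | 0.16 × 0.460 + 0.64 = 0.714 | 0.64 | 10% |
| 0.7 | 0.09 × 0.460 + 0.51 = 0.551 | 0.51 | 8% (7.5%) |

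The 95% CI half-width for a difference is 2.002 × 5 × √(variance × 2/30). At r = 0.5 this is 2.40 points for change scores and 2.24 with adjustment.

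If SD 5 and r = 0.5 held in the enrolled sample itself, the change-score factor would be 2(1 − r) = 1.00 against 1 − r² = 0.75. The half-widths would then be 2.58 and 2.24, and the saving 25%.

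**The case against.** The best defence is that this is a pilot with feasibility as the primary outcome, sized on the basis that "the sample size estimation is not based on power analysis but according to rule of thumb". The scales are secondary, descriptive reporting is respectable, and model form and covariates are usually left to a SAP, which is not shown. Summaries will exist for all three arms, so control-arm change will be visible beside aromatherapy change, and section 8.1 already promises intervals where they apply.

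Much of this stands. Avoiding hypothesis tests is reasonable, and silence on a covariate alone would be no finding. But section 8.1.2 is not silent: it fixes change against an MIC as the focus, and it does so without the contrast that the objective asks for. An adjusted difference with an interval is estimation, so it fits a pilot that avoids testing. Reading two arm means side by side gives neither an interval nor a baseline-adjusted estimate.

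Three stronger readings are tempting and are not supported:

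- A reader might infer that within-arm change will be presented as efficacy. The text does not say so, and the control arm will be reported too.
- A reader might infer that regression to the mean could by itself carry an arm past an MIC. A mean fall of 0.8 to 1.4 points makes that unlikely. Entry also requires a clinical diagnosis of depression, so selection is not on PHQ-9 alone, and a higher source mean shrinks the fall.
- A reader might infer that adjustment is worth a third more patients (1/0.75 = 1.33). That holds only if SD 5 and r = 0.5 describe the enrolled sample. With selection at PHQ-9 ≥ 5 under the assumed source values, the equivalent is about 8 to 15% more patients (0.551/0.51 = 1.08; 0.865/0.75 = 1.15).

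**Conclusion.** The point holds. As written, section 8.1.2 does not answer the objective of comparing aromatherapy with routine care, because change from baseline against an MIC cannot distinguish added benefit from change expected in every arm.

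The part due to the entry threshold is modest: 0.8 to 1.4 PHQ-9 points, and 13 to 22% of participants passing an assumed 5-point threshold. This rests wholly on the assumed mean, SD, correlation and selection rule. Natural recovery would add to it by an amount that the protocol does not allow one to estimate. The argument for a between-arm difference does not depend on these sizes.

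The precision gain over change scores is a secondary benefit: 8 to 13% lower variance under the same assumptions, and 25% only in the special case shown. Since these are secondary outcomes of a pilot, this is a change that should be made, not one that threatens the feasibility conclusions.

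**What to change.** In section 8.1.2 or the SAP, state that for each scale the aromatherapy-minus-control and aromatherapy-minus-CBT differences will be reported at week 4 and at one month after the intervention. Each comes from a linear model with arm and the baseline value of that scale, with a 95% CI and no P-value. Keep within-arm change and the proportion reaching the MIC as description by arm, give the between-arm difference in that proportion, and say that within-arm change will not be read as a treatment effect. State the MIC used for each scale, and report the residual SD for planning the main trial.

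The cost is a few lines of text and one simple model per scale and visit. No further data or patients are needed, because the baseline values are already collected.

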Using VFT as an activation task, researchers investigated frontal lobe function in patients with PSD, and found that the fNIRS oxygen-hemoglobin score value was negatively correlated with 17-item Hamilton Rating Scale for Depression (HAMD-17) total score, and there was a significant difference between the oxygen-hemoglobin score value of the nondepressed group and that of the depressed group (41). These results suggest that fNIRS has potential in diagnosing PSD. Nevertheless, more studies are required to ascertain the validity, sensitivity, and specificity of fNIRS as a diagnostic tool for PSD. However, beyond the study by Koyanagi et al. (41), no other studies have replicated this finding. Additionally, there is still a lack of near-infrared research specifically focusing on this unique subset of depression, PSD. Therefore, while fNIRS shows promise as an objective measurement, it cannot yet be considered a definitive diagnostic tool for PSD. More studies are required to ascertain its validity, sensitivity, and specificity.

This study employs two comparators: Cognitive Behavioral Therapy (CBT) and non-active conventional treatment. CBT is included as a comparator due to its well-established efficacy and widespread acceptance as a standard treatment for various forms of depression, including PSD. The inclusion of a non-active conventional treatment group allows for the assessment of the absolute effects of aromatherapy, offering a baseline to observe changes attributable solely to the aromatherapy intervention without the influence of active therapeutic elements.

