##### Conventional rehabilitation treatment

4.2.1.1

Serving as the baseline comparison, all participants will receive standard rehabilitation treatments, including physical therapy, occupational therapy, acupuncture and medication management, to meet basic rehabilitation needs. This control group allows us to assess the additional benefits of CBT and Aromatherapy Inhalation interventions on top of standard care.

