##### CBT group

4.2.2.2

The CBT group will participate in a comprehensive rehabilitation regimen that integrates conventional treatments with Cognitive Behavioral Therapy (CBT), administered by trained psychotherapists. The inclusion of CBT aims to improve mental health and coping strategies, ensuring a comprehensive treatment protocol that addresses both the physical and psychological aspects of recovery for the control group. Participants will receive standard rehabilitation treatments in addition to CBT sessions conducted twice weekly, each lasting 30 minutes, over four weeks. The interventions include:

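### The efficacy message attached to the aromatherapy-versus-CBT non-inferiority comparison does not depend on the usual-care arm, so two treatments with no effect over usual care can pass and be presented as potentially effective

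*Protocol article*

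**What the plan says.** Protocol article, section 8.1.2, plans non-inferiority tests of aromatherapy against CBT. The margin is "typically set at a 10% margin", without saying what the 10% is taken of. The rule reads: "aromatherapy is considered non-inferior if the difference in improvement between CBT and aromatherapy falls within this margin". The same bullet closes with the message to be drawn: "This analysis will highlight the potential of aromatherapy as an effective complementary therapy".

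The usual-care arm has a stated purpose elsewhere. Section 4.2.1.1 says: "This control group allows us to assess the additional benefits of CBT and Aromatherapy Inhalation interventions on top of standard care". Section 1.1 likewise says that this arm lets the absolute effect of aromatherapy be assessed. In section 8.1.2, however, the clinical scales are to be summarised and compared with minimal important changes only: "Given the limited sample size, inferential analysis will be avoided".

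The efficacy of CBT is taken from outside the trial. Section 1.1 says: "CBT is included as a comparator due to its well-established efficacy and widespread acceptance". The CBT arm receives "CBT sessions conducted twice weekly, each lasting 30 minutes, over four weeks" (section 4.2.2.2).

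**The concern.** Being close to CBT says something about effectiveness only if CBT, as delivered here, does better than usual care. That amount is 2 × 4 = 8 sessions, or 8 × 30 min = 4 hours. The protocol gives no CBT-versus-usual-care effect for it that a margin could be set to preserve, and section 4.2.1.2 treats the usefulness of CBT in stroke rehabilitation as something this trial is to evaluate. All arms receive the same rehabilitation programme and may also improve spontaneously. Improvement in every arm with little separation between arms is therefore a plausible outcome, and it is the case in which a two-arm non-inferiority comparison misleads.

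At stake is how the secondary results are reported. Aromatherapy could be described as non-inferior to CBT and potentially effective while neither treatment differs from the usual-care arm of the same trial.

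**Working it through.** **Inputs from the protocol article**
- Section 4.5: about 30 per group, 10% dropout, 33 recruited per group, 99 in total. Check: 30 × 1.10 = 33 and 3 × 33 = 99. Dividing by 0.9 instead gives 34, which makes no difference here. 33 × 0.9 = 29.7, so about 30 per arm are analysed.
- Section 4.3.2: the PHQ-9 runs from 0 to 27.
- Section 8.1: "with P < 0.05 considered statistically significant". Sidedness is not stated.

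**Assumptions not in the protocol**
- SD of PHQ-9 change: 5, with a range of 4 to 6.
- Margin M on the PHQ-9: 0.3 points (10% of an assumed 3-point gain in the CBT arm), 1.2 points (10% of an assumed baseline of 12) or 2.7 points (10% of the 27-point range).

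**Method.** If neither treatment adds anything to usual care, the true CBT–aromatherapy difference is 0, which lies inside any positive margin. The standard error is SE = SD × √(2/n) = 5 × √(2/30) = 1.29. The wording of section 8.1.2 allows three readings of a pass:
- 95% confidence bound clears the margin: Φ(M/SE − 2.00), approximately
- point estimate no worse than the margin: Φ(M/SE)
- point estimate within the margin on both sides: 2Φ(M/SE) − 1

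**Chance that two inert treatments pass (n = 30 per arm, SD 5; SD 4 to 6 in brackets)**

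| M | M/SE | Confidence bound | Point, no worse | Point, both sides |
|---|---|---|---|---|
| 0.3 | 0.23 | 4% (4–4%) | 59% (58–61%) | 18% (15–23%) |
| 1.2 | 0.93 | 14% (11–20%) | 82% (78–88%) | 65% (56–75%) |
| 2.7 | 2.09 | 54% (40–73%) | 98% (96 to over 99%) | 96% (92–99%) |

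If the 10% means percentage points on a responder outcome, with equal rates of 20% to 50% and 30 per arm, two inert treatments pass 78–83% of the time by point estimate and 12–16% by confidence limit.

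**Effect of requiring CBT to beat usual care.** Suppose a pass is read as efficacy only when CBT also beats usual care at two-sided 0.05. With CBT inert, that condition alone is met in the favourable direction 2.5% of the time, so the false efficacy reading cannot exceed about 2.5%. A simulation of 400,000 draws (SD 3 to 6; margins of 0.5, 1.0 and 2.7 points; 30 or 33 per arm) gave 0.4–2.5% with the point rule and 0–1.8% with the confidence limit.

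**Cost of that condition.** With 30 per arm its power is Φ(d/√(2/30) − 1.96). This is about 21%, 49% and 87% for assumed standardised CBT effects of d = 0.3, 0.5 and 0.8.

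**The case against.** The strongest reply is that the usual-care comparison is not absent. Objective 3 compares aromatherapy with routine treatment as well as CBT. Section 8.1.2 summarises every scale at each time point, and section 8.1 foresees confidence intervals and effect sizes where applicable. A reader could therefore see whether CBT separated from usual care. This stands as far as it goes, but the plan does not tie the conclusion to that display. This is not a detail left to an analysis plan that is not shown: the article itself states both the rule and the message drawn from it.

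Four stronger readings are tempting, and the document does not support them.
- A reader might infer that a pass is declared to show that aromatherapy works. The sentence speaks only of highlighting potential, which is softer, although it is written to apply whatever the data show.
- A reader might infer that a false pass would wrongly trigger a full-scale trial. The criteria in section 4.5 are recruitment, adherence and completion, and section 4.3.1 adds a safety threshold. No efficacy result is among them.
- A reader might take the 59%, 82% and 98% as the pass rates of the written rule. Section 8.1.2 speaks of tests, which points to a confidence bound and the much lower first set of figures. The text does not settle which reading applies.
- A reader might infer that two inert treatments pass as often as two equally effective ones for any margin. That holds for a margin fixed in scale points. It fails if the 10% is taken of CBT's own gain: under the one-sided point rule with SD 5, a 3-point gain gives 59% and a 6-point gain gives Φ(0.6/1.29) = 68%.

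It can also be said that a significance condition on CBT adds inference to a pilot that says it avoids it, and that its power is low. That is fair. The condition is the more debatable part of the remedy, and showing all three differences does not depend on it.

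**Conclusion.** The point holds in limited form. The efficacy message in section 8.1.2 rests on a comparison that leaves out the one arm able to show whether either treatment works, so two treatments with no effect over usual care can pass and be presented as potentially effective. The chance ranges from about 4% (confidence bound, 0.3-point margin) to 98% (one-sided point estimate, 2.7-point margin). Those figures assume an SD of 5 and 30 analysed per arm, and the spread mainly reflects what the protocol leaves open: the base of the margin and the form of the decision. Defining the margin or moving to a confidence bound would change the pass rate but would not supply the missing link to usual care. The consequence is a misleading secondary message and not a wrong progression decision. The change is worth making because it is cheap and uses an arm already randomised.

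**What to change.** In section 8.1.2:
1. Report aromatherapy minus usual care, CBT minus usual care and aromatherapy minus CBT, each with a 95% confidence interval.
2. Take any efficacy signal from aromatherapy minus usual care.
3. State that closeness to CBT is not read as evidence of effectiveness unless CBT minus usual care shows benefit in this trial.
4. Replace the closing sentence on aromatherapy's potential with wording that follows from items 2 and 3.

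The cost is a change of wording and two further between-arm estimates from data already collected, using intervals that section 8.1 already foresees. The downside is that at about 30 per arm the condition in item 3 will often not be met (power about 49% at an assumed standardised effect of 0.5), so the pilot will seldom support an efficacy reading from the CBT comparison. If the trial team prefers no formal condition, dropping the non-inferiority test and describing the three differences with their intervals would also remove the problem.
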